#### Primary endpoint

Sensitivity and other test parameters, such as specificity, positive predictive value (PPV) and negative predictive value (NPV), of the qPCR test will be calculated with respect to a composite reference standard including any of the other tests (induced sputum and gastric aspirate Xpert Ultra and MGIT culture, stool Ultra or TB-LAM in HIV-positive individuals).

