Despite its increasing availability in high TB burden settings, the 4^th^ generation Xpert® Ultra in sputum (Cepheid Inc., Sunnyvale, CA, USA) confirms TB in 90% of adult cases with HIV-infection[11] and 62–89% of culture-positive pediatric cases [12]. While mycobacterial culture is the accepted reference standard for assessing novel TB diagnostic tests, it only confirms TB in 10–50% of children clinically diagnosed with pulmonary TB [13–16] and about half of PLHIV starting on anti-tuberculosis treatment (ATT).

To address this diagnostic gap, researchers at Baylor College of Medicine (Houston, Texas, USA) developed a novel, stool bead-based, real-time quantitative PCR (qPCR) diagnostic test for TB. A pilot study evaluating this qPCR have shown its ability to increase TB case confirmation among adults in Eswatini and children in Tanzania with clinically diagnosed, bacteriologically negative TB (by sputum Xpert) by 12% and 19%, respectively. This study also points to the test’s ability to predict TB treatment failure [17]. In Eswatini, the detection of *M.tb* DNA in the stool after 2 months of ATT was associated with treatment failure, death, or DR-TB (RR 3.5, 95% CI: 1.32- 9.64; *p* = 0.015) [17]. Thus, this qPCR platform provides an important opportunity to explore the utility of a qPCR for treatment monitoring via quantification of *M.tb* burden in stool. In addition, this test could be combined with novel approaches to assess *M. tb* viability using molecular mycobacterial load assays [18].

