### Endpoints

#### Definitions

For analysis, the participants in the pediatric cohort will be classified as ‘confirmed tuberculosis’, ‘unconfirmed tuberculosis’ and ‘unlikely tuberculosis’ according international consensus pediatric endpoint definitions [22].  “TB case” definition will include both ‘confirmed’ and ‘unconfirmed’ tuberculosis. “Unlikely TB” will be used as reference for specificity (see Table 2).

**Table 2 Tab2:** Definitions for the pediatric cohort

**TB case**	**“Confirmed tuberculosis”**	*M. tb* to be laboratory-confirmed (culture or NAAT-based assay) from at least 1 specimen or positive urine LAM
	**“Unconfirmed tuberculosis”**	Bacteriological confirmation not obtained and at least 2 of the following: 1. symptoms/signs suggestive of tuberculosis, 2. chest radiograph consistent with tuberculosis, 3. close tuberculosis exposure or immunologic evidence of *M. tuberculosis* infection 4. positive response to tuberculosis treatment (requires documented positive clinical response on tuberculosis treatment—no time duration specified)
**Not TB case**	**“Unlikely tuberculosis”**	bacteriological confirmation not obtained and criteria for “unconfirmed tuberculosis” not met

For the adult cohort participants will be classified as “bacteriologically confirmed TB” or “clinically diagnosed TB”. “TB case” definition will be equivalent to decision to start treatment irrespective of bacteriological confirmation so it will include both “bacteriologically confirmed TB” and “clinically diagnosed TB”

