### Data synthesis and analysis

We will summarize demographic characteristics of the samples and will perform a descriptive analysis of endpoints and other relevant clinical variables. Quantitative variables will be summarized using means, standard deviation, median and interquartile range. Categorical variables will be analysed using frequencies and proportions. We will analyze the mechanisms that contribute to missing data, which will guide subsequent imputation methods to address missingness. An accuracy analysis will be performed for both study groups (children and PLHIV) with bacteriologically confirmed tuberculosis as a reference standard and qPCR assay on stool as the index test under evaluation. We will calculate sensitivity *(primary endpoint)* and other test parameters: specificity, PPV and NPV, of the qPCR test compared to composite reference standard that includes any of the other tests positive (including induced sputum and gastric aspirate Xpert Ultra and MGIT culture, stool Ultra or LF-LAM). We will also calculate sensitivity (and other parameters: specificity, PPV and NPV) of the qPCR test *(secondary endpoint)* with respect to a clinical case definition. Accuracy will also be assessed for stool qPCR and each of the other microbiological confirmation tests separately against the clinical case definition (*secondary endpoint)*, in order to compare the performance of each test.

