## Discussion

This study is designed to evaluate a new diagnostic test that aims to improve molecular confirmation of TB as well as provide a new monitoring tool for treatment response in children and PLHIV. To date, studies using stool as a target sample have been done with already existing molecular tests like Xpert and Xpert Ultra using stool, but few of those studies propose novel molecular platforms for validation or exclusively include the vulnerable populations of intended use (children or PLHIV with presumptive TB). Therefore, the relevance of this study relies not only on the use of stool as a sample for bacteriological confirmation, but also on the molecular non-Xpert based approach to it, as there is need for improvement molecular stool diagnostics. Further, the design is aligned with the latest WHO guidelines on diagnosis and management of TB in children and adolescents that, for the first time, include stool as a valid sample for TB testing. In fact, apart from the classical approach of using culture in a respiratory sample as a reference standard, we will assess the performance of this new diagnostic test against a robust composite reference standard that includes culture and Xpert Ultra in respiratory samples, Xpert Ultra in stool and LF-LAM in urine and against clinical diagnosis. In this way, we will both maximize the bacteriological confirmation and estimate the potential increase in bacteriological confirmation in those cases that start treatment in the absence of bacteriologic confirmation. It will also allow to see the contribution of each single TB test to bacteriological confirmation, including the expected additionality of que novel stool-based qPCR (all other test negative but qPCR positive).

Another relevant strength in the study design is the two week and two-month longitudinal follow-up to verify baseline disease classification in participants who do not initiate treatment. This will play a relevant role in both increasing the number of confirmed cases (after resampling if persistence of symptoms), but also in the reliability of the specificity estimations (only those who have tested negative at baseline, who did not start treatment and who do not present symptoms after 2 months will be classified as “unlikely TB”).

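### The protocol gives two unreconciled reference groups for specificity, and no rule keeps unconfirmed or clinically diagnosed TB out of the non-cases for adult specificity, PPV or NPV

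*Protocol article*

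**What the plan says.** Under Primary endpoint, the quantities are "Sensitivity and other test parameters, such as specificity, positive predictive value (PPV) and negative predictive value (NPV), of the qPCR test", and they "will be calculated with respect to a composite reference standard including any of the other tests". Data synthesis and analysis repeats the rule: "specificity, PPV and NPV, of the qPCR test compared to composite reference standard that includes any of the other tests positive". That section attaches the primary label to sensitivity only: "We will calculate sensitivity *(primary endpoint)* and other test parameters".

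Under Definitions, the pediatric category Unlikely TB "will be used as reference for specificity". Table 2 defines that category as "bacteriological confirmation not obtained and criteria for “unconfirmed tuberculosis” not met". The Discussion takes the same line: it rests the reliability of specificity on participants who were negative at baseline, untreated and free of symptoms at two months.

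For adults, Definitions names only bacteriologically confirmed and clinically diagnosed TB. The third category, not TB, appears only in the Methods part of the Abstract.

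Two further statements bear on the point. Under Secondary endpoints, all four parameters are also computed against the TB case definition, which includes unconfirmed and clinically diagnosed TB. The Discussion says that the study will show "the expected additionality of que novel stool-based qPCR (all other test negative but qPCR positive").

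**The concern.** The negatives of the bacteriological composite are a mixture: participants judged not to have TB, and participants judged to have TB whom no other test could confirm. The study's hypothesis is that qPCR is positive in part of the second group. In the pilot, qPCR raised confirmation among adults and children "with clinically diagnosed, bacteriologically negative TB (by sputum Xpert) by 12% and 19%, respectively".

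If all composite-negatives are non-cases, those detections lower specificity and PPV. The better the test performs as hypothesised, the worse these two parameters look, while the Discussion reports the same participants as a gain.

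If Unlikely TB is the reference group, pediatric specificity escapes this. Because the protocol states both rules, an analyst could follow either and claim compliance. If the choice is left until data are seen, the result could influence the rule.

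**Working it through.** **Sample size, to confirm that it is not touched.** The inputs from Power and sample size are sensitivity 80%, half-width 7.5% (children) and 7% (adults), and confirmed proportion 8.5% and 20%. A 95% two-sided level is assumed.
- Children: 1.96² × 0.8 × 0.2 / 0.075² = 109.3, so 110 cases; 110 / 0.085 = 1294.1, so 1295, as stated.
- Adults: 1.96² × 0.8 × 0.2 / 0.07² = 125.4, so 126 cases; 126 / 0.20 = 630. The stated 650 is slightly larger and gives a half-width of 6.9%.

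Both calculations use sensitivity alone, so the choice of non-cases does not enter.

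**Who is a non-case under each rule.**

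| Parameter | Primary endpoint; Data synthesis and analysis | Definitions; Discussion |
|---|---|---|
| Specificity, children | all composite-negatives | Unlikely TB only |
| Specificity, adults | all composite-negatives | no group named |
| PPV, NPV, both cohorts | all composite-negatives | no group named |

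**Size under the literal composite rule, children.** Inputs: 1295 × 0.085 = 110 confirmed, so 1185 composite-negative; sensitivity 80%, giving 88 true positives. Assumptions: a fraction f = 20-40% of composite-negatives is unconfirmed TB; 19% of these are qPCR-positive (pilot yield); specificity is 99% in Unlikely TB.

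The formulas are: extra detections x = 1185 × f × 0.19; false positives in Unlikely TB, FP = 0.01 × 1185 × (1 − f); specificity = 1 − (x + FP) / 1185; PPV = 88 / (88 + x + FP).
- f = 20%: x = 45.0, FP = 9.5; specificity 95.4%, PPV 61.8%. Counting x as TB, PPV = (88 + 45.0) / (88 + 45.0 + 9.5) = 93%.
- f = 40%: x = 90.1, FP = 7.1; specificity 91.8%, PPV 47.5%. Counting x as TB, PPV = (88 + 90.1) / (88 + 90.1 + 7.1) = 96%.

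**If the yield were half the pilot's (9.5%).**
- f = 20%: x = 22.5; specificity = 1 − 32.0/1185 = 97.3%, PPV = 88/120.0 = 73%.
- f = 40%: x = 45.0; specificity = 1 − 52.1/1185 = 95.6%, PPV = 88/140.1 = 63%.

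**NPV moves the other way.** With f = 20%, 1130 composite-negatives are qPCR-negative and 22 confirmed cases are missed, so NPV against the composite is 1130 / 1152 = 98%. Against TB case, only the 938 qPCR-negative children with Unlikely TB are true negatives, so NPV is 938 / 1152 = 81%. With f = 40% the figures are 1088 / 1110 = 98% and 704 / 1110 = 63%.

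**Adults.** Inputs: 130 confirmed, 520 composite-negative, 104 true positives. Assumptions: f = 10-30%, yield 12%, specificity 99% in those without TB.
- f = 10%: x = 6.2, FP = 4.7; specificity 97.9%, PPV 90%.
- f = 30%: x = 18.7, FP = 3.6; specificity 95.7%, PPV 82%.

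**Second illustration, using the Background's confirmation shares.** The Background says that culture confirms 10-50% of clinically diagnosed children and about half of treated PLHIV. Taking these as the share confirmed by the composite, with an assumed 98% specificity in those without TB:
- Children: 110 to 991 unconfirmed and 21 to 188 of them qPCR-positive; specificity 96.4% down to 83.8%, PPV 67.5% down to 31.4%.
- Adults: 130 clinically diagnosed and about 16 qPCR-positive; specificity 95.5%, PPV 81.6%.

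**The case against.** The strongest reply is that there is no conflict. The Definitions sentence follows directly on the TB case definition, and could describe only the secondary analysis, leaving the composite for the primary one. The study would then report two prespecified reference standards side by side, a recognised way of handling an imperfect reference. This does not fully succeed. Against TB case, Unlikely TB is already the only non-case group in children, so confined to that analysis the sentence would add nothing. The Discussion also ties specificity to that group without limiting it to the secondary endpoint.

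Much else in the reply stands. A reader might infer that the settled primary analysis will score the expected extra cases as errors. The documents do not support that:
- Only sensitivity is labelled primary, and it alone sizes the study. No target is given for specificity or PPV.
- For pediatric specificity, Definitions states the opposite rule; if it governs, the pediatric loss of specificity does not arise.
- The TB case analysis credits these detections as true positives, and qPCR-only positives are to be reported as additionality.

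The magnitudes are also soft. The unconfirmed shares of 20-40% and 10-30% and the 99% and 98% specificities are not in the protocol. The pilot yield was measured beyond sputum Xpert alone. The composite adds culture, stool Ultra and LF-LAM, so the yield beyond it may be lower.

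**Conclusion.** The inconsistency stands. Two different non-case groups are stated for pediatric specificity. For adult specificity, and for PPV and NPV in both cohorts, the only stated rule leaves unconfirmed or clinically diagnosed TB among the non-cases.

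Under that literal rule and the first set of assumptions, pediatric specificity would read about 95-92% instead of 99%, and PPV about 62-48% instead of 93-96%. The adult effect is smaller. These figures illustrate direction and order of size and are not predictions; a lower yield beyond the full composite shrinks them without reversing them.

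The point concerns parameters other than the labelled primary one. It calls for reconciling the text and does not undermine the design: sensitivity and sample size are unchanged, and the secondary analysis supplies part of the remedy.

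**What to change.** In Primary endpoint and in Data synthesis and analysis, state who the non-cases are for each cohort and each parameter:
- **Specificity under the primary endpoint:** Unlikely TB in children, as Definitions already says; not TB in adults, with that category carried from the Abstract into Definitions.
- **Unconfirmed and clinically diagnosed TB:** left out of that denominator, with their qPCR positivity reported separately as additional yield.
- **PPV and NPV:** taken from the TB case analysis.
- **Composite-negative specificity, PPV and NPV:** kept as labelled sensitivity analyses.

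Sensitivity against the composite stays as it is. The cost is wording, with no new data or participants, and it should be settled before data are analysed.

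There are downsides to disclose. The specificity denominator is smaller: in children, 1185 × 0.8 = 948 to 1185 × 0.6 = 711 under the 20-40% assumption. Leaving out the cases that are hardest to classify may slightly favour specificity, which is why the composite-negative estimate should remain visible. NPV against TB case will read lower than against the composite.

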#### Secondary endpoints

Sensitivity and other parameters (specificity, PPV and NPV) of the qPCR test with respect to the “TB case” definition.

Accuracy of stool qPCR and each of the other microbiological confirmation tests separately against the “TB case” definition.

Treatment response by monitoring time to negativity of the qPCR on stool after treatment initiation and comparing with standard mechanisms for treatment monitoring (symptom resolution and culture negativity on sputum) as well as predicting outcome.

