Stool Xpert MTB/RIF was reported to have a limit of detection (LOD) greater than 267 CFU/mL [19]. In contrast, when using a bead-based DNA isolation kit designed for soil (MP Fast DNA, MPBio), the LOD was lowered to 96 Mtb Colony Forming Units (CFU) per 50 mg of stool (95% CI 84–105 CFU), which approximately represents 5 CFU/mL [20, 21]. There is still little evidence about the performance of Xpert Ultra on stool, but a recent Cochrane review reports a sensitivity of around 60% against culture (varying from 39 to 100% including data from unpublished cohorts) [12]. For Xpert Ultra the LOD has been lowered to 16 CFU/mL. This shows some room for improvement, for which we expect the qPCR, combined with the DNA isolation kit developed for stool specimens, to present with a higher sensitivity than Xpert® Ultra. Therefore, we propose a diagnostic evaluation to assess the performance of this stool-based qPCR for TB bacteriological confirmation among PLHIV and children with the hypothesis that it may present an increased sensitivity for TB diagnosis compared to currently recommended microbiological tests.

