## Methods

### Aim and objectives

The primary objective of the Stool4TB study is to evaluate the diagnostic performance of the stool bead-based real-time quantitative PCR (qPCR) platform for TB diagnosis in children < 8 years and PLHIV compared to a composite reference standard that includes sputum (induced sputum and/or gastric aspirate in children) and stool Xpert Ultra, sputum (induced sputum and/or gastric aspirate in children) culture, and urine LF-LAM (among people living with HIV).

As a secondary objective, we will compare the diagnostic accuracy of the novel stool qPCR assay to the other tests against clinical diagnosis and a bacteriological reference standard [22]. We will also evaluate the quantitative stool qPCR platform as a tool to monitor treatment response in these two populations. Samples collected from these cohorts will be used to develop a biorepository of well characterized samples to enable future TB related research as an exploratory objective.

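### The head-to-head of stool qPCR against the other tests uses a TB case reference that already contains those tests, so the comparators gain specificity, PPV and sensitivity by construction

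*Protocol article*

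**What the plan says.** The Aim and objectives section sets a secondary objective to "compare the diagnostic accuracy of the novel stool qPCR assay to the other tests against clinical diagnosis and a bacteriological reference standard". The Secondary endpoints section turns this into "Accuracy of stool qPCR and each of the other microbiological confirmation tests separately against the" TB case definition. The Data synthesis and analysis section repeats it, calls the reference a clinical case definition, and gives the purpose: "in order to compare the performance of each test".

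The Definitions section (Table 2) settles what that reference contains in children. A TB case is confirmed or unconfirmed tuberculosis, and confirmed means *M. tb* is "laboratory-confirmed (culture or NAAT-based assay) from at least 1 specimen or positive urine LAM". The specificity group, unlikely tuberculosis, requires "bacteriological confirmation not obtained and criteria for “unconfirmed tuberculosis” not met".

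In adults, TB case is equated with the decision to start treatment and is said to include bacteriologically confirmed TB. The Discussion adds that only participants who tested negative at baseline can be classed as unlikely TB.

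Two places imply that the study qPCR is outside confirmation. The Primary endpoint section builds the composite from the other tests, and the Discussion counts participants positive only on qPCR as added yield.

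**The concern.** This is incorporation bias, and it acts on one side of the comparison only. A positive comparator makes a child a TB case, so it can never be scored as a false positive, and all of its positives enter its own sensitivity numerator. A positive qPCR counts as correct only if another test or the clinical criteria agree. A true case found by qPCR alone that misses the clinical criteria is scored as a qPCR false positive. The same lone detection by Ultra would have made that participant a case.

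The study hypothesis is comparative: the Background says of the qPCR that "it may present an increased sensitivity for TB diagnosis compared to currently recommended microbiological tests". The primary endpoint describes qPCR alone, so this is the listed endpoint that compares accuracy between tests. The label clinical case definition hides that the reference contains the comparators. The other reference named in the secondary objective, a bacteriological standard, has the same problem if it is the composite.

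**Working it through.** **The plan's own figures.** No stated figure belongs to this endpoint. The sample size for the primary endpoint can be checked, assuming two-sided 95% confidence.
- Children: 1.96² × 0.8 × 0.2 / 0.075² = 109.3, so 110 confirmed cases. 110 / 0.085 = 1294.1, rounded up to 1295, as stated.
- Adults: 1.96² × 0.16 / 0.07² = 125.4, so 126 cases. 126 / 0.20 = 630, against 650 stated. This is mild conservative rounding and has no bearing on this point.

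**General result.** Let R be TB case, T a comparator and Q the qPCR. T lies wholly inside R.
- Comparator: sensitivity = P(T)/P(R); specificity = PPV = 100%.
- qPCR: sensitivity = P(Q and R)/P(R).
- If both tests have the same positivity rate, the sensitivity deficit is P(Q outside R)/P(R) and the specificity deficit is P(Q outside R)/P(not R). Both are zero or positive, so the direction does not depend on the data.

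**Illustration with identical tests.** These inputs are assumptions, not taken from the article: every test has sensitivity 50% and specificity 98%; the clinical criteria have sensitivity 70% and specificity 85%; true prevalence is 15 to 25%; tests are conditionally independent. R is any comparator positive or clinical criteria met. I use three comparators (respiratory Ultra, culture, stool Ultra), or four with LAM.

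At 20% prevalence with three comparators:
- Any comparator positive: with TB 1 − 0.5³ = 0.875; without TB 1 − 0.98³ = 0.0588.
- Scored as a case: with TB 0.875 + 0.125 × 0.7 = 0.9625; without TB 0.0588 + 0.9412 × 0.15 = 0.2000.
- P(R) = 0.2 × 0.9625 + 0.8 × 0.2000 = 0.3525.
- P(T) = P(Q) = 0.2 × 0.5 + 0.8 × 0.02 = 0.1160.
- P(Q and R) = 0.1 × 0.9625 + 0.016 × 0.2000 = 0.09945, so P(Q outside R) = 0.01655.
- Comparator: sensitivity 0.1160/0.3525 = 32.9%, specificity 100%, PPV 100%.
- qPCR: sensitivity 0.09945/0.3525 = 28.2%, specificity 1 − 0.01655/0.6475 = 97.4%, PPV 0.09945/0.1160 = 85.7%.

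| Comparators in reference | Sensitivity deficit, prevalence 15–25% | Specificity deficit |
|---|---|---|
| 3 | 5.2 to 4.3 points | 2.4 to 2.7 points |
| 4 | 4.5 to 3.5 points | 2.2 to 2.4 points |

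With three comparators and all tests 99.5% specific, the sensitivity deficit is 2.2 to 2.3 points. With all tests 100% specific it is 1.0 to 1.3 points.

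**Anchored to the stated confirmation rates.** The illustration implies more confirmed TB than the 8.5% planned for children (three comparators, 15% prevalence: 0.15 × 0.875 + 0.85 × 0.0588 = 18%). I therefore also solved prevalence so that confirmed TB equals 8.5% in children (three comparators) and 20% in adults (four). Assumed ranges: true sensitivity 40 to 60%, specificity 98 to 100%, 60 to 90% of unconfirmed true TB and 10% of test-negative non-TB meeting the clinical criteria. The spurious qPCR deficit is 0.2 to 9.7 points of sensitivity and about 0 to 2.1 of specificity in children, and 0.1 to 5.9 and about 0 to 2.4 in adults. The largest values occur at 98% specificity, where the solved prevalence in children is only 3.0 to 3.6% and most confirmed cases would be false.

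**The case against.** Several objections have force.

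- **Size.** A reader might infer a deficit of about 9 points in sensitivity and 3.5 to 5 in specificity. That follows from putting a single comparator in the reference (9.3 to 9.4 and 3.5 to 4.7 points on the same inputs), but the definition contains all of them, which roughly halves the sensitivity gap. Also, children enter with TB symptoms, and symptoms are one of the criteria for unconfirmed tuberculosis. If the clinical criteria were 90% sensitive, the three-comparator gap would be 3.4 to 4.6 points. In the worked example most of the specificity gap is the comparator being raised from a true 98% to 100%; qPCR falls only to 97.4%.
- **Adults.** A reader might infer that 100% comparator specificity is guaranteed in adults too. The operative wording is the treatment decision, so a test-positive adult who is never treated could be a non-case. With true sensitivity 60% and specificity 99%, and 5 to 10% of positives not counted, comparators would show about 99.2 to 98.5% specificity against 98.2 to 97.5% for qPCR. The statements that the definition includes bacteriologically confirmed TB, and that non-cases tested negative, point back to 100%.
- **Is qPCR really outside?** Table 2 says NAAT-based assay, and the study qPCR is a NAAT. If it counted, the asymmetry would vanish (both tests 24.5% and 100% in a children's example with true sensitivity 60% and specificity 99%), but qPCR would then sit in its own reference. The text favours exclusion without saying so.
- **Reach.** A reader might infer that the hypothesis cannot be tested fairly at all. The article does not support that: the primary endpoint is a different analysis, qPCR-only yield is to be reported, and the Discussion mentions a culture reference ("apart from the classical approach of using culture in a respiratory sample as a reference standard"). That no endpoint repeats the culture reference may be condensation for publication.
- **Pairing.** Scoring the tests separately does not exclude a paired contrast. That can be left to the analysis plan and is no finding.

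None of this removes the core: in children, comparator specificity and PPV are set by definition.

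**Conclusion.** The point holds as a bias written into the secondary comparison. With qPCR outside the reference, comparator specificity and PPV against TB case are 100% by definition in children and nearly or fully so in adults, and comparator sensitivity gains as well. The direction is certain for equally accurate tests. The size is not: about 3.5 to 5 points of sensitivity and 2 to 3 of specificity under the illustrative inputs with three or four comparators, shrinking towards zero as test specificity approaches 100%. These figures rest on assumed accuracies and conditional independence, not on values in the article. The primary endpoint is not affected in this way. Severity: should be fixed, as a secondary endpoint.

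**What to change.** 1. State that the study qPCR is excluded from confirmed tuberculosis and from TB case.
2. Do not report or compare a comparator's specificity or PPV against a definition that contains that comparator.
3. For the head-to-head of the NAATs, above all stool qPCR against stool Ultra, use one common reference containing neither test: respiratory culture, or TB case rebuilt without both compared tests.

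This needs a wording change and analysis of data already being collected. The costs are fewer reference positives and wider intervals; the Background itself says culture confirms only 10–50% of children clinically diagnosed with pulmonary TB. A culture reference may also favour respiratory Ultra, which is run on the same respiratory samples, so the stool-to-stool contrast is the cleanest. In adults, a rebuilt TB case cannot fully remove test results that informed the treatment decision, so culture is the simpler choice there.
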